## Abstract

**Background:**

Cardiac amyloidosis (CA) is a rare disease that can lead to poor quality of life, conduction disorders, arrhythmia, heart failure, and even death. Fortunately, specific treatments that can modify the natural history of the disease and the disease outcomes are now available. However, data on the prevailing patient management procedures and long-term outcomes of CA are scarce.

**Objective:**

The Healthcare Amyloidosis European Registry (HEAR) is 34-centre registry initiated in France and structured for European expansion through the French Clinical Research Infrastructure Network’s Group for Research on Amyloidosis and Care Excellence and the European Clinical Research Infrastructure Network. We expect to include 8500 patients between January 2021 and December 2027.

**Methods:**

The HEAR has been designed to capture detailed demographic, clinical, laboratory, imaging, and therapeutic data from both suspected and confirmed cases of all cardiac amyloidosis subtypes, including wildtype transthyretin amyloidosis, variant transthyretin amyloidosis, light-chain amyloidosis, and rarer forms. This comprehensive approach has been designed to (i) improve our understanding of real-world diagnostic pathways, treatment practices, and patient outcomes and (ii) incorporate patient-centred innovations. To enhance the patient-centred nature of the registry, patient-reported outcome measures (PROMs) will be systematically collected.

**Conclusions:**

By addressing diagnostic pathways, real-world management and PROMs and by applying technological innovations and European scalability, the next-generation HEAR is establishing itself as a valuable resource for clinical research, public health interventions, and better patient care in the field of CA.

**Supplementary information:**

The online version contains supplementary material available at 10.1186/s13023-025-04062-y.

## Introduction

Cardiac amyloidosis (CA) is a rare disease characterized by the continuous accumulation of infiltrating, insoluble fibrillar proteins in the extracellular matrix of various organs, including the kidneys, nerves, liver, heart, and skeletal muscles [1]. The prevalence of CA in Europe is not known [2]; however, data from the Transthyretin Amyloidosis Outcomes Survey (THAOS) suggest that the prevalence of wild-type (non-hereditary) TTR amyloidosis (ATTRwt) in North America and Europe ranges from 13 to 18 cases per million [3]. Cardiac involvement is frequently observed for three types of systemic amyloidosis: (i) amyloid light chain amyloidosis (caused by excess monoclonal light chain production by a plasma cell clone), (ii) hereditary transthyretin (TTR) amyloidosis (ATTRv, inherited in an autosomal dominant manner and caused by the deposition of mutant TTR protein), and (iii) wild-type (non-hereditary) TTR amyloidosis (ATTRwt).

For a patient with amyloidosis, the prognosis typically depends on the state of cardiac involvement [4, 5]; unfortunately, CA is often diagnosed late in the course of the disease, when the prognosis is poor. ATTRwt mainly affects men over the age of 60, whereas ATTRv affects both women and men and usually appears between the ages of 40 and 60 (depending on the mutation). This diagnostic delay is due to several factors: (i) the level of amyloid infiltration needed to generate symptoms; (ii) the amyloid fibrils’ speed of accumulation; (iii) a low level of awareness of CA among physicians; and (v) the lack of simple diagnostic tools (biomarkers, imaging, etc.) for early diagnosis. The absence of early diagnosis, the heterogeneity of the multisystem expression of amyloidosis, and the complexity of patient management result in diagnostic delays, failure to treat organ damage, and degradation of the patient’s quality of life (QoL) and chances of survival [4, 6–8].

Hence, physicians must better recognize the cardiac and extracardiac signs of amyloidosis, characterize the disease’s clinical and biochemical presentations and their times of onset, improve diagnostic tools, and adopt standardized patient management procedures. International and national registries and observatories [8] are important tools for improving the quality of care [3, 6, 9–13]. These tools make it possible to spread information to the entire community with regard to care practices and the latter’s changes over time and impacts on public health. This is particularly true in the field of cardiology. Thus, it has been demonstrated that the countries that implemented national registers a long time ago (such as Sweden) have improved their practices more quickly than countries that took this step later (such as the United Kingdom) [14].

Several national and international registries have been developed, in order to better characterize CA and related conditions. Among the most prominent are the THAOS [3, 13], the Systemic Amyloidosis in Europe (EURAMY) network [15], the UK-based National Amyloidosis Centre [16], all of which have significantly improved the understanding of the disease’s natural history, genotype-phenotype correlations, and therapeutic outcomes. When compared with existing registries, the Healthcare European Amyloidosis Registry (HEAR) presented here constitutes an innovative, comprehensive approach (Table 1).

**Table 1 Tab1:** Comparison of the HEAR with existing cardiac amyloidosis registries

Registry	THAOS	NAC Database	EURAMY	HEAR
Amyloidosis subtypes included	ATTR-only	All subtypes (ATTR, AL, others)	AL mainly	All subtypes (ATTR, AL, others)
Suspected cases included	No	No	No	Yes
PROMs collected	Optional/inconsistent	?	No	Yes (AmyloAFFECT-QOL, MLHFQ, KCCQ)
Centralized imaging	No	No	No	Yes (AI-based via MIRACL.ai)
PREMs collected	No	No	No	Planned (AI patient chatbot)
Linkage to national databases	No	No	No	Planned
Linkage to clinical research and trial networks	No	?	No	GRACE F-CRIN/E-CRIN
Governance	Industry-sponsored	Single-centre academic	Centre-dependent	Multicentre academic
Scalability and future strategy	Terminated	Will include several centres in UK	Terminated	European expansion

THAOS: Transthyretin Amyloidosis Outcomes Survey; NAC: National Amyloidosis Centre; EURAMY: Systemic Amyloidoses in Europe; HEAR: Healthcare Amyloidosis European Registry; ATTR: Transthyretin amyloidosis; AL: Light chain amyloidosis; PROM: MLHFQ: Minnesota Living Heart Failure Questionnaire; KCCQ: Kansas City Cardiomyopathy Questionnaire; PREM: patient-reported experience measures; MIRACL.ai: Multimodality Imaging for Research and Analysis Core Laboratory and Artificial Intelligence; AI: Artificial Intelligence; GRACE: Group for Research on Amyloidosis and Care Excellence: F-CRIN: French Clinical Research Infrastructure Network; E-CRIN: European Clinical Research Infrastructure Network

Existing registries differ in scope, geographic coverage, inclusion criteria, and long-term follow-up strategies. Furthermore, most existing datasets are limited to specific clinical settings, national frameworks, or pharmaceutical-sponsored initiatives; this potentially creates gaps in harmonized data collection across Europe. To address this need, the HEAR was initiated as an independent registry with scope for expansion across Europe. The goal is to provide a unified, collaborative platform for the collection of standardized clinical, genetic, and treatment-related data across multiple countries. This should support research, care optimization, and policy-making in the field of amyloidosis, accelerate improvements in practice, and thus extend survival times for patients [14].

In order to bridge this knowledge gap and collect representative data, we have initiated the Healthcare Amyloidosis European Registry (HEAR) in France and are planning to extend it to other European countries. The HEAR is sponsored by Heart’s Foundation (Vincennes, France) and is already Europe’s largest multicentre registry of CA. Its primary objective is to characterize the natural history of CA by capturing detailed clinical and diagnostic data at the time of diagnosis, documenting current treatment practices, and assessing patient outcomes in real-world settings. Building on this foundation, collaborative efforts seek to advance the understanding of this rare disease, generate critical evidence, and thus inform future guidelines for optimal diagnosis and management. The present report outlines the design and implementation of the HEAR, which has been developed in France as the new, operational platform for the French Clinical Research Infrastructure Network (F-CRIN)’s Group for Research on Amyloidosis and Care Excellence (GRACE). The F-CRIN https://www.fcrin.org/en) supports research, expertise and clinical investigation networks in targeted medical fields linked to the European Clinical Research Infrastructure Network (E-CRIN, https://ecrin.org/). Through the GRACE, the F-CRIN and the E-CRIN, the HEAR will benefit from expertise in harmonizing data collection tools, support in regulatory alignment across European countries, and access to a network of national scientific coordinators (clinical trial units and research infrastructures) across Europe.

## Methods

### Objectives of the registry

The HEARs primary objective is to describe the demographic, clinical, laboratory data and imaging characteristics and the QoL of patients referred for suspected CA and patients with a confirmed diagnosis of CA. It will thus provide insights into real-world diagnosis pathways.

The registry’s secondary objectives are to (i) estimate the prevalence and incidence of the different types of amyloidosis and their changes over time, (ii) describe the cardiac and extracardiac cardiac signs and their time of appearance, depending on the diagnosis, (iii) describe the course of care (diagnosis pathway and time) and its change over time, (iv) assess the quality of diagnostic tools (biomarkers, imaging, etc.) and algorithm diagnosis [17], (v) describe patient QoL and well-being, using the AmyloAFFECT-QOL [7] (a validated, amyloidosis-specific questionnaire), the Minnesota Living Heart Failure Questionnaire (MLHFQ), and the Kansas City Cardiomyopathy Questionnaire (KCCQ), (vi) describe the disease prognosis and its change over time, (vii) describe cardiological and specific treatments and their benefits and side effects, (viii) assess the number and reasons for hospital admissions and medical and surgical interventions, (ix) link to other databases (e.g. health insurance databases), and (x) share good practice and thus evaluate and optimize the quality of healthcare for patients with CA in France.

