### Design and sampling

The HEAR is a French, multicentre, observational registry for patients with suspected or confirmed CA. We expect to include 8,500 patients between July 2021 and December 2027. The registry will comprise retrospective, retroprospective and prospective cohorts.

Firstly, the HEAR RETROSPECTIVE cohort will comprise deceased patients with confirmed diagnosis of CA, who met the inclusion criteria and were treated at the centre after 2009. The data from this cohort will enable us to characterize the natural history of the disease.

Secondly, the HEAR RETROPROSPECTIVE cohort will comprise live patients with a confirmed diagnosis of CA and real-life follow-up from the date of inclusion, who have been treated after 2009 and are still being monitored at the centre. The patients will be asked to give their written, informed consent for the retroprospective and prospective collection of their personal data.

Thirdly, the HEAR PROSPECTIVE cohort will comprise patients referred to the participating centres for suspected CA. The real-life data from this cohort will enable us to characterize (i) diagnostic pathways for patients with suspected amyloidosis and (ii) changes in the management of CA. The patients will be asked to give their written, informed consent for the prospective collection of their personal data.

We are collecting demographic, clinical, laboratory, imaging, and QoL data (via the systematic completion of the AmyloAFFECT-QOL questionnaire, the MLHFQ and the KCCQ) and diagnostic data at baseline for all registered patients, by using a structured electronic case report form (e-CRF)). We will also collect data on patient management by the cardiologists and specific details of treatments. Lastly, we intend to collect in-hospital data on outcomes (deaths, cause of death, and hospital readmissions) annually.

Furthermore, the HEAR will include a digital health component through the development of an artificial-intelligence-powered patient chatbot designed to (i) provide educational support and personalized guidance, (ii) explain quality-of-life questionnaires in accessible terms, (iii) facilitate the completion of patient-reported outcome measures (PROMs), (iv) collect patient-reported experience measures), and (v) promote health literacy and patient empowerment.

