### Participating centres

The lead investigator (an experienced researcher and a cardiologist at the French National Cardiac Amyloidosis Reference Centre) identified 34 hospitals and invited them to participate in the HEAR; all accepted (Appendix A and Fig. 1). The 34 participating centres are representative of France’s geographic and ethnic diversity. Each centre has been asked to register consecutive patients. The distribution of patient inclusions by centre as of March 1^st^, 2024, is shown in Fig. 2. Four centres had not started recruitment at that date. Lastly, it should be noted that we intend to extend the HEAR to other European countries.

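### Secondary objective (i) promises prevalence and incidence of amyloidosis types, but registry inclusions alone cannot support population rates or their trends

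*Protocol article*

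**What the plan says.** The second paragraph of *Objectives of the registry* lists ten secondary objectives. The first is to "estimate the prevalence and incidence of the different types of amyloidosis and their changes over time". The ninth, listed separately, is linkage to other databases such as health insurance data; Table 1 shows linkage to national databases as planned.

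The sources of cases are set out in three sections:

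- *Participating centres*: the lead investigator "identified 34 hospitals and invited them to participate in the HEAR; all accepted". Centres are asked to register consecutive patients and are described as representative of the country's geography and ethnic mix. At the count of 1 March 2024, "Four centres had not started recruitment at that date".
- *Design and sampling*: the PROSPECTIVE cohort "will comprise patients referred to the participating centres for suspected CA". The RETROSPECTIVE cohort is made up of deceased patients with confirmed CA who "were treated at the centre after 2009". The RETROPROSPECTIVE cohort is made up of living patients with confirmed CA "who have been treated after 2009 and are still being monitored at the centre".
- *Definition, inclusion, and exclusion criteria*: adults with suspected or confirmed CA and French social security coverage. The main exclusion is refusal.

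The inclusion period appears twice. The Abstract has "We expect to include 8500 patients between January 2021 and December 2027"; *Design and sampling* has "We expect to include 8,500 patients between July 2021 and December 2027".

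**The concern.** Population prevalence and incidence need a numerator that counts all cases in a defined population, or a known fraction of them, and a denominator for that population. The stated entry rules give a numerator made up of consenting or deceased patients who reached particular hospitals. A rate built on it would measure referral and registration as well as disease.

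The trend is exposed in the same way. A rise in registered cases could come from more disease, more suspicion among physicians, more referral to these hospitals, or more hospitals taking part. The Discussion says the registry also aims to raise awareness of CA, and the Introduction names low awareness as one reason for late diagnosis. The registry may therefore itself change how many cases are found.

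This matters because the Introduction says that the prevalence of CA in Europe is not known. A figure published by a large registry under the heading of prevalence or incidence could be taken as the missing estimate.

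**Working it through.** The article gives no prevalence or incidence figure, so there is no stated result to reproduce. The check is whether the entry rules can yield what the objective names.

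**1. Who can enter the numerator**

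| Group of patients | Captured? | Source in the article |
|---|---|---|
| Referred to one of the 34 centres with suspected CA, agrees | Yes, PROSPECTIVE | Design and sampling |
| Confirmed CA, treated at a centre after 2009, deceased | Yes, RETROSPECTIVE | Design and sampling |
| Confirmed CA, treated after 2009, alive, still monitored, agrees | Yes, RETROPROSPECTIVE | Design and sampling |
| Confirmed CA, treated after 2009, alive, no longer monitored at the centre | No cohort fits | Design and sampling |
| Managed only at hospitals outside the 34 | No | Participating centres; Design and sampling |
| Refuses | No | Exclusion criterion |
| Amyloidosis without suspected cardiac involvement | No | Inclusion criteria |

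The last four rows follow from the stated rules and do not depend on what the article leaves out. The last also shows that the objective's wording, types of amyloidosis, is wider than the cardiac population enrolled.

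**2. Effect on a level**

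Let c be the share of all cases in the source population that the registry captures. Then:

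rate from registry counts = c × true rate.

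The article does not give c. The statement that the centres reflect France's geographic and ethnic diversity concerns the mix of patients, not the share of cases covered, so c cannot be inferred from it.

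**3. Effect on a trend**

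For two periods:

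ratio of registry rates = (c₂ / c₁) × ratio of true rates.

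The trend is unbiased only if c is the same in both periods. Referral habits, awareness and the set of active centres can each change c. On 1 March 2024, 34 − 4 = 30 centres had started. How much the other four would add depends on their share of the caseload. The article's text does not state that share, and Fig. 2, which shows inclusions by centre, is not available here. The size of the distortion therefore cannot be calculated.

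**4. What the design can estimate**

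The PROSPECTIVE cohort has an internal denominator: consecutive patients referred for suspected CA. The proportion diagnosed with each CA type is

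p(type) = number with that type / number of consecutive referrals.

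This needs no catchment population. Its change over time can be followed if the set of centres is held fixed or otherwise accounted for.

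**5. Start date**

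January 2021 to December 2027 is 7 × 12 = 84 months. July 2021 to December 2027 is 6 + 6 × 12 = 78 months. The two statements of the inclusion period differ by six months for the same 8,500 patients.

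**The case against.** The strongest reply has four parts.

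- **The route to population rates is already planned.** Linkage to health insurance databases is objective (ix) and could supply a population denominator and a check on completeness. This stands. A reader might infer that prevalence and incidence cannot be estimated within this programme at all; the documents do not support that. What remains is that the article does not connect objective (i) to the linkage.
- **This is a condensed article.** A denominator, a person-time definition and a completeness method could sit in the full protocol or analysis plan, and their absence here is not a fault. That also stands. But an analysis plan cannot add the cases that the entry rules leave out, so the difficulty goes beyond missing detail.
- **Late centres can enter earlier cases.** A centre that opens late may register deceased patients treated after 2009 and living ones still monitored. Counts by date of diagnosis therefore need not jump when a centre opens. This stands in part: the back-entry misses living patients who have left the centre. It does rule out one tempting step, which is to read the ratio of 34 to 30 centres as the inflation of incidence. That ratio would describe inclusions only, and only if all centres had equal volume.
- **Objective (i) is partly achievable.** Consecutive referral gives relative frequencies by type. This stands and is the basis of the change proposed.

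**Conclusion.** The point holds in a limited form: as described, registry inclusions alone do not support population prevalence or incidence of amyloidosis types, or trends in them. This rests on the stated routes of entry and needs no assumed figure. The direction is partly clear, because incomplete capture lowers a rate computed over the whole population. The size is not: neither the captured share nor the caseload of the late centres is given, and any numerical correction factor would be invented.

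It concerns one of ten secondary objectives. The primary descriptive objective is unaffected.

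The start-date conflict is real but minor and separate. A reader might infer that the six months shift every rate in proportion. They do not: the 8,500 mixes deceased, already diagnosed and merely suspected patients, so dividing it by the window gives only enrolment speed. Incidence by calendar year of diagnosis, or prevalence on a given date, does not depend on the length of the inclusion window.

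**What to change.** - Restate objective (i) along these lines: *describe the relative frequency of cardiac amyloidosis types among consecutive patients referred for suspected CA (PROSPECTIVE cohort), and its change over time, with trends accounting for centre activation*. Restricting comparisons to centres active throughout the periods compared is one way to do this; terms for centre and time in the analysis are another.
- Report population prevalence and incidence only through the planned health-insurance linkage (objective ix), with a defined source population and an assessment of how completely cases are captured.
- Use one inclusion start date in the Abstract and in *Design and sampling*.

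The rewording and the date correction need no new data collection beyond what is planned. The price is that population rates wait for the linkage, and that trends may rest on fewer centres and so be less precise.

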### Design and sampling

The HEAR is a French, multicentre, observational registry for patients with suspected or confirmed CA. We expect to include 8,500 patients between July 2021 and December 2027. The registry will comprise retrospective, retroprospective and prospective cohorts.

Firstly, the HEAR RETROSPECTIVE cohort will comprise deceased patients with confirmed diagnosis of CA, who met the inclusion criteria and were treated at the centre after 2009. The data from this cohort will enable us to characterize the natural history of the disease.

Secondly, the HEAR RETROPROSPECTIVE cohort will comprise live patients with a confirmed diagnosis of CA and real-life follow-up from the date of inclusion, who have been treated after 2009 and are still being monitored at the centre. The patients will be asked to give their written, informed consent for the retroprospective and prospective collection of their personal data.

Thirdly, the HEAR PROSPECTIVE cohort will comprise patients referred to the participating centres for suspected CA. The real-life data from this cohort will enable us to characterize (i) diagnostic pathways for patients with suspected amyloidosis and (ii) changes in the management of CA. The patients will be asked to give their written, informed consent for the prospective collection of their personal data.

We are collecting demographic, clinical, laboratory, imaging, and QoL data (via the systematic completion of the AmyloAFFECT-QOL questionnaire, the MLHFQ and the KCCQ) and diagnostic data at baseline for all registered patients, by using a structured electronic case report form (e-CRF)). We will also collect data on patient management by the cardiologists and specific details of treatments. Lastly, we intend to collect in-hospital data on outcomes (deaths, cause of death, and hospital readmissions) annually.

Furthermore, the HEAR will include a digital health component through the development of an artificial-intelligence-powered patient chatbot designed to (i) provide educational support and personalized guidance, (ii) explain quality-of-life questionnaires in accessible terms, (iii) facilitate the completion of patient-reported outcome measures (PROMs), (iv) collect patient-reported experience measures), and (v) promote health literacy and patient empowerment.

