### Definition, inclusion, and exclusion criteria

We apply the diagnostic criteria for CA given in the European Society of Cardiology’s 2021 expert consensus [17]. The criteria for patient inclusion in the HEAR are as follows: age 18 or over, referral for suspected CA or a confirmed diagnosis of CA, and coverage by the French social security system. The main exclusion criterion was refusal to participate in the registry. Patients included in the HEAR do not receive any financial compensation.

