### Longitudinal follow-up

Given that the study is observational, patients will be followed up according to each centre’s standard procedures; the patient’s management will not be modified and no additional visits will be required. However, vital status and clinically significant events will be collected for all patients included in the HEAR RETROSPECTIVE cohort. In the absence of a visit to the centre or inclusion in the HEAR PROSPECTIVE cohort (see below), the vital status (alive or dead) of patients will be confirmed successively by (i) consulting the centre’s appointment scheduling software, (ii) phoning the patient or a relative if the patient had not attended the participating centre after the study set-up, (iii) contacting the patient’s general practitioner by phone or by post, and (iv) contacting the town hall corresponding to the patient’s last known address by phone or by post.

For all patients included in the HEAR PROSPECTIVE cohort, vital status (alive or dead) will be checked annually. If a year goes by without the collection of data (i.e. failure to visit the study centre), the investigators will seek to document vital status and events that occurred in the previous year by carrying out the procedures described above for the HEAR RETROSPECTIVE cohort.

In accordance with the current French legislation and regulations, adverse events (whether serious or not) will be notified to the competent authorities by the study investigators. These events will be recorded by the investigators throughout the study, using the dedicated sections of the e-CRF.

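### Deceased and living confirmed patients enter under different rules, so survival counted from diagnosis in the pooled confirmed cohorts can be biased, in a direction and by an amount the article does not settle

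*Protocol article*

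**What the plan says.** Design and sampling sorts confirmed patients into two cohorts by vital status and gives each its own entry condition.

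- The RETROSPECTIVE cohort "will comprise deceased patients with confirmed diagnosis of CA, who met the inclusion criteria and were treated at the centre after 2009". No condition of continuing follow-up is attached.
- The RETROPROSPECTIVE cohort takes living confirmed patients "who have been treated after 2009 and are still being monitored at the centre". Consent is also sought: "The patients will be asked to give their written, informed consent for the retroprospective and prospective collection of their personal data".
- The PROSPECTIVE cohort is for patients referred on suspicion of the disease, so a former patient with an established diagnosis does not belong there.

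The general criteria (Definition, inclusion, and exclusion criteria) are "age 18 or over, referral for suspected CA or a confirmed diagnosis of CA, and coverage by the French social security system". They contain no monitoring condition that would carry over to the deceased. The same section adds: "The main exclusion criterion was refusal to participate in the registry". Centres are asked to register patients consecutively (Participating centres).

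Secondary objective (vi) is to "describe the disease prognosis and its change over time" (Objectives of the registry). The Longitudinal follow-up section describes how vital status is established for the RETROSPECTIVE cohort when a patient has not been seen; one step is "phoning the patient or a relative if the patient had not attended the participating centre after the study set-up".

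**The concern.** Take a confirmed patient treated in 2014 who later moved or stopped attending. If dead, this patient fits the RETROSPECTIVE definition. If alive, the patient fits no cohort as defined. Entry is thus conditional on the outcome that objective (vi) is meant to describe.

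Merging the two confirmed cohorts does not restore a complete source population, because the rule shuts out living former patients and not deceased ones. A survival curve from diagnosis on the merged data would then mix patients selected because they died with patients selected because they lived and stayed in care. If the selection differs between diagnosis eras, part of any difference in prognosis between eras would be artefact. This matters in practice: the Discussion already presents a before-and-after comparison of survival around the availability of tafamidis as an example of the registry's value.

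**Working it through.** **Plan's own figure.** There is none to reproduce. The article gives no mortality, retention or capture figure, and the planned 8,500 patients are not split by cohort.

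**Entry rules side by side, for a confirmed patient treated at the centre after 2009**

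| Status now | Still monitored | No longer monitored |
|---|---|---|
| Dead (monitored or not up to death) | RETROSPECTIVE | RETROSPECTIVE |
| Alive | RETROPROSPECTIVE, with consent | No cohort |

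The top-right cell is read from the absence of a monitoring condition for the deceased; the article does not say it in so many words.

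**Effect on the pooled share dead.** Let D be the true share dead, a the share of deaths captured and m the share of living patients enrolled (still monitored and consenting). All three are assumed.

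Shown share dead = D·a / (D·a + (1 − D)·m)

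It exceeds D when a > m, equals D when a = m, and falls below D when a < m.

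With D = 50%:

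- a = 100%, m = 90%: 0.50 / (0.50 + 0.45) = 52.6%
- a = 100%, m = 80%: 0.50 / (0.50 + 0.40) = 55.6%
- a = 100%, m = 70%: 0.50 / (0.50 + 0.35) = 58.8%
- a = 90%, m = 90%: 0.45 / (0.45 + 0.45) = 50.0%
- a = 90%, m = 80%: 0.45 / (0.45 + 0.40) = 52.9%
- a = 70%, m = 90%: 0.35 / (0.35 + 0.45) = 43.75%

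Other values of D, with a = 100% and m = 90%, 80%, 70%:

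- D = 30%: 32.3%, 34.9%, 38.0%
- D = 70%: 72.2%, 74.5%, 76.9%

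**Effect on a time trend.** If a and m are the same in every diagnosis era, the selection is the same in every era. An artefactual difference between eras of equal true mortality needs the capture shares to differ. Suppose D = 40% in both eras, all deaths are captured, and 30% of survivors are lost in the early era against 5% in the recent one. The shown shares are 0.40 / (0.40 + 0.42) = 48.8% and 0.40 / (0.40 + 0.57) = 41.2%, about 7.5 points apart. That result leans on equal D. Early patients have had longer to die. At D = 80% or 90%, losing 30% of survivors gives 0.80 / 0.94 = 85.1% or 0.90 / 0.97 = 92.8%, a shift of 5.1 or 2.8 points.

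These are crude shares dead, used to show direction and rough scale. They are not survival estimates.

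**The tracing text.** Longitudinal follow-up says that vital status, alive or dead, is confirmed for the RETROSPECTIVE cohort, and the steps include telephoning the patient. Design and sampling limits that cohort to the deceased. Both cannot hold as written. The follow-up section names the RETROSPECTIVE and PROSPECTIVE cohorts and never the RETROPROSPECTIVE one, so it is unclear which rule the living confirmed patients follow.

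**The case against.** The strongest reply is that direction is not established. A patient who moves away and dies elsewhere is easily missed, and the annual outcome collection in Design and sampling is described as in-hospital. If such deaths are often unknown to the centre, the excess of deaths shrinks or reverses, as the 43.75% case shows. This stands in full. A reader might infer that the pooled cohorts necessarily over-represent deaths; the document does not support that.

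A reader might also infer that tracing worsens the problem, by keeping patients found dead and dropping those found alive. The section concerns patients already included and is not written as a screening step. If anything it suggests that some RETROSPECTIVE patients may be alive, which would partly close the gap. What can be said is that the two sections conflict.

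A third inference would be that the registry manufactures an improving prognosis of about 8 points. That needs loss of contact to grow with time since diagnosis, which the document does not state, along with complete death capture and equal mortality across eras.

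It can also be said that the formal criteria carry no monitoring condition and that registration is consecutive. But patients enter through the cohorts, and no cohort is described for a living former patient. Finally, time origin, censoring and delayed entry may be handled in an analysis plan that is not shown. That is fair, and silence on them is not the point here. The point is the stated entry rule.

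**Conclusion.** The concern holds in conditional form. The cohort definitions make entry depend on vital status, and pooling the confirmed cohorts does not remove this. Survival from diagnosis, or prognosis over time, estimated on the pooled data can therefore be biased.

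Deaths are over-represented only if deaths among former patients are captured more completely than survivors are enrolled. The consent step for the living makes that plausible, and deaths unknown to the centre work against it. The size cannot be computed from the document. Under the assumed values, at 50% truly dead, the shown share runs from 43.75% to 58.8%. A spurious trend needs capture shares that differ by era.

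A reader might go on to doubt the tafamidis comparison cited in the Discussion. Its methods are not shown, so nothing can be concluded about it. The objective affected is secondary; the primary objective in the Methods section is descriptive. This is an improvement worth making at low cost, not a flaw that undermines the registry.

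**What to change.** 1. **Analysis population for survival.** Estimate survival and its change over time from RETROPROSPECTIVE patients with delayed entry (left truncation) at the date of inclusion, plus PROSPECTIVE patients from referral or diagnosis. Use the deceased-only RETROSPECTIVE cohort for description, not for survival estimates or era comparisons. This needs only analysis wording and data already being collected. The cost is lower precision and little information on early-era survival. It also assumes that, at a given time since diagnosis, patients still in care at inclusion have the same later hazard as those who left; otherwise the result applies to patients who remain in care.

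2. **Reconcile the text.** State whether the RETROSPECTIVE cohort is deceased-only, as in Design and sampling, or may include living patients, as Longitudinal follow-up implies. Say which vital-status procedure applies to the RETROPROSPECTIVE cohort. This costs an edit.

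3. **Optional, where a centre can do it.** Apply one entry rule to all confirmed patients treated after 2009, whatever their vital status or current monitoring. Censor at the date last known alive. Report, by diagnosis year and vital status, how many were eligible but not enrolled. With a = m within each era the formula returns the true share. It is optional because reaching former patients across 34 centres adds site work and needs a consent route.
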